This study is therefore designed to extend the previous study [12] by examining the effect of proximal (i.e., forearm first and wrist second) priority robotic priming and impairment-oriented training (PRI) and distal (i.e., wrist first and forearm second) priority robotic priming and impairment-oriented training (DRI) with a larger sample size (i.e., *n* = 20 in each group). We hypothesize that the PRI and DRI groups will both improve significantly on normalized muscle tone, sensorimotor impairment, upper limb function, self-efficacy, and quality of life from preintervention to postintervention and that the improvement will be maintained at the follow-up assessment. In addition, this study will compare the relative effects between PRI and DRI. We hypothesize that the PRI group will achieve better proximal UE motor ability and that the DRI group will achieve better distal UE motor ability.

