### Primary outcome measurements

The **UE-FMA** is used to assess motor impairment of body function, including ranges of motion of the UE joints, and grasping, coordination, and speed of UE movement. The UE-FMA is scored on a 3-point ordinal scale (0 = cannot perform, 1 = perform partially, 2 = perform fully), with a total score between 0 and 55. A higher UE-FMA score means better motor performance and less impairment.

The **Medical Research Council Scale (MRC)** measures muscle power of the affected UE joints. The MRC is scored on a 6-point ordinal scale (0 = plegic, 5 = resisted to maximal strength, full power compared with the unaffected side).

The **Revised Nottingham Sensory Assessment (rNSA)** is used to assess sensory impairment, including pressure, temperature, light touch, kinesthetic sense on the shoulder, elbow, wrist, and hand, and stereognosis. The rNSA is scored on a 3-point ordinal scale (0 = absent, 1 = impaired, 2 = normal), with a total score of 48. The rNSA has acceptable inter-rater reliability.

The **Wolf Motor Function Test (WMFT)** assesses functional motor ability of the UE with 15 functional tasks. The patient is requested to perform tasks as quickly as possible and use the affected side in task performance. Average time (WMFT-Time) and functional ability score (WFMT-FAS) are reported.

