### Statistical analyses

The Student *t* test and *χ*^2^ will be used to analyze differences in baseline characteristics and outcome measures between the two groups. Two-way repeated-measures of analysis of variance will be used to determine the intervention effects. The within-subject factor is time (i.e., pretest, posttest, and follow-up assessment), and the between-subject factor is group (i.e., PRI and DRI). A post hoc Tukey test will be used when a group × time interaction or a main effect is observed. An *α* level of .05 is set for all statistical comparisons. Partial eta squared (*η*^2^) will also be estimated to determine the group difference for each outcome measure. Predictors of PRI and DRI outcomes will be estimated with the chi-square automatic interaction detector (CHAID) method. Data analyses will be performed using SPSS Statistics 18.0 software (IBM Corp, Armonk, NY, USA).

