## Discussion

In recent decades, rehabilitation robots have been rapidly developed and play a critical role in improving UE function after stroke, offering dedicated training that can be coupled with other rehabilitation programs provided by rehabilitation therapists [18]. The effects of combined bilateral robotic priming techniques with task-oriented approaches have been validated in several studies [12, 19]. IOT emphasizes remediation of reduction in UE function after stroke, including deficits in motor control and impaired sensorimotor function of the arm, wrist, and hand [9], but few studies have investigated the combined bilateral robotic priming therapy with IOT. This study is planned to replicate the previous pilot study [12] to examine empirically the immediate and follow-up effects of the combination of bilateral RT with IOT on sensorimotor function of UE in chronic stroke.

For patients with motor control problems, the sequence of relearning of movement from proximal to distal body parts is a topic of debate and needs scientific examination in a systematic way [15]. The proximal joints of the UE, such as the shoulder and scapula, are assumed to be responsible for stability and support of the arm during reaching for targets, and the distal joints (e.g., wrist and hand) are responsible for functional manipulation in activities of daily life. However, distal-emphasized RT (i.e., training on wrist and forearm movements) combined with functional task practice was found to be more effective on muscle strength and quality of movement during functional activities than proximal-emphasized RT (i.e., shoulder and elbow movements) combined with functional task practice [19]. It is possible that distal robotics provide both mechanical stability and repetitive movement practice of the distal joints at the same time, while coordinated distal manipulation of the UE is based on stability from the proximal joints in therapist-facilitated interventions for stroke patients.

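### The proximal/distal hypothesis is tied to no regional endpoint or contrast, and on the UE-FMA and WMFT overall scores its predicted opposite effects offset fully or partly

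*Protocol article*

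**What the plan says.** The Background (Bilateral robotic priming before impairment-oriented training) gives two hypotheses. The first is that both groups improve from before to after treatment and hold the gain at follow-up. The second is the only one that compares the groups: "the PRI group will achieve better proximal UE motor ability and that the DRI group will achieve better distal UE motor ability".

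Primary outcome measurements names four instruments:

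- **UE-FMA** is described by its overall range: "with a total score between 0 and 55".
- **WMFT** covers 15 tasks and is summarised overall: "Average time (WMFT-Time) and functional ability score (WFMT-FAS) are reported".
- **Medical Research Council Scale (MRC)** "measures muscle power of the affected UE joints". No total or average is stated.
- **Revised Nottingham Sensory Assessment (rNSA)** is a sensory scale, which the article says "is used to assess sensory impairment, including pressure, temperature, light touch, kinesthetic sense on the shoulder, elbow, wrist, and hand, and stereognosis".

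None is given a proximal or distal score, and neither is any motor measure under Secondary outcome measurements. Statistical analyses sets out a repeated-measures ANOVA: "The within-subject factor is time (i.e., pretest, posttest, and follow-up assessment), and the between-subject factor is group (i.e., PRI and DRI". Partial eta squared "will also be estimated to determine the group difference for each outcome measure".

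**The concern.** Both groups receive the same robot modes, the same treatment time and the same impairment-oriented training. The planned difference is the order of the modes. The hypothesis therefore predicts a regional signal with opposite signs and gives no reason to expect a difference over the whole limb. The outcomes and model, as stated, contain no region.

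A score that adds proximal and distal items receives a gain for PRI from one part and a gain for DRI from the other. If the hypothesis is true, the group-by-time test on that score is likely to be non-significant, and readers could conclude that sequence does not matter. A significant total would not show which region produced it. Regional scores chosen after the data are seen would leave open where the forearm belongs.

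**Working it through.** **The plan's own figure.** The sample size is 40, or 20 per group. It cannot be reproduced, because the article gives no effect size, SD or power and attributes the size to limits on recruitment. For orientation, the standardized difference detectable with 80% power at two-sided 0.05 is (1.960 + 0.842) × √(2/20) = 0.886 (normal approximation).

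**Inputs from the article.** n = 20 per group; α = 0.05.

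**Assumptions.** The test is two-sided (the article does not say). The proximal effect is +p and the distal effect −q, in SDs of change, with positive values favouring PRI. The two subscores have equal SDs and correlation ρ of 0.3 to 0.7. A two-group t test on change stands in for the group-by-time test. The total is modelled as the sum of two regional parts, which fits the UE-FMA directly and the WMFT by analogy.

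**Formulas.**

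- Total score: d = (p − q) / √(2(1 + ρ))
- Proximal change minus distal change: d = (p + q) / √(2(1 − ρ))
- Power: noncentral t with 38 df and noncentrality d × √(20/2)

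**One case in full.** With p = 0.8, q = 0.4 and ρ = 0.5, the total has d = 0.4/√3 = 0.231 and power 11%. The contrast has d = 1.2/√1 = 1.20 and power 96%.

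**Range over ρ = 0.3 to 0.7.**

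| Proximal / distal effect (SD) | d, total | Power, total | Power, contrast |
|---|---|---|---|
| +0.5 / −0.5 | 0 | 5% | 74–98% |
| +0.8 / −0.8 | 0 | 5% | 99% or more |
| +0.8 / −0.5 | 0.19–0.16 | 8–9% | 92–99.9% |
| +0.8 / −0.4 | 0.25–0.22 | 10–12% | 88–99.8% |
| +0.8 / −0.2 | 0.37–0.33 | 17–21% | 74–98% |
| +0.8 / 0 | 0.50–0.43 | 27–33% | 55–89% |

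One subscore tested alone has 34% power at 0.5 SD and 69% at 0.8 SD, before any multiplicity adjustment.

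**Unequal SDs.** Suppose the proximal subscore has 1.5 or 2 times the SD of the distal one, with equal and opposite standardized effects and ρ = 0.5. Total-score power is then 6% or 9% at 0.5 SD, and 9% or 15% at 0.8 SD. Cancellation is no longer exact, but power stays low.

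The last row of the table shows a limit of the contrast: it can be significant when only one region differs.

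**The case against.** A reader might infer that every primary outcome is a whole-limb score, that the effects always cancel, and that the trial cannot detect its own hypothesis. The documents do not support that.

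- MRC is described by joint with no total, so it could be split by region from the data as collected. The rNSA is sensory: it does not test a motor hypothesis, and that hypothesis predicts no opposing effects within it.
- Exact cancellation needs effects that are equal in score units. Otherwise the offset is partial, as the table shows.
- The UE-FMA wording gives a range and does not say that only the total will be analysed. A full protocol or analysis plan, not shown, may define subscores.
- Overall scores and the time effect suit the first hypothesis. Replacing all the primary outcomes would leave that hypothesis without one.
- A reader might also infer that the trial changes its meaning of proximal, because the Discussion has the phrase "distal-emphasized RT (i.e., training on wrist and forearm movements". That phrase describes the robots of a cited study. For its own groups, the article consistently uses forearm-first and wrist-first.
- Partial eta squared carries no sign, but it is an additional statistic and group means will show direction.

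All of these stand, and they narrow the point without removing it. The article itself states the hypothesis, the outcomes and the factors of the model, and these do not meet. That is more than detail left to another document. Proximal ability is also never defined as an outcome, so the place of the forearm items is open.

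**Conclusion.** The concern holds in this limited form: the between-group hypothesis has no named regional endpoint or contrast, and on the UE-FMA and WMFT overall scores the predicted effects offset fully or partly. In every scenario where both predicted effects are present with equal SDs, total-score power is between 5% and 21%, while the contrast has 74% or more. The figures rest on assumed effects of 0.2 to 0.8 SD and correlations of 0.3 to 0.7, none of which the article supplies. The direction of the finding does not depend on exact cancellation. The within-group hypothesis is unaffected.

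**What to change.** Keep the existing overall outcomes for the within-group hypothesis. For the between-group hypothesis, prespecify the following before outcome data are examined, including at the interim analyses mentioned under Data management and quality:

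1. Proximal and distal UE-FMA subscores, stating which one holds the forearm items, with a matching grouping of MRC joints as support.
2. One group contrast, PRI minus DRI in (proximal change minus distal change), at the postintervention assessment.
3. The two directional subscore comparisons after it, with Holm adjustment, because the contrast alone can be driven by one region.
4. Signed mean differences with 95% CIs, alongside partial eta squared.

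The cost is small, since the items are already collected. Subscores have fewer items and may be less reliable than the total, and Holm adjustment can lower the single-subscore power shown above. Trial status estimates that recruitment would start on December 1, 2020, before the article appeared in September 2021. If recruitment has begun, the change must be recorded as an amendment.

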## Methods and design

### Participants

The inclusion criteria are age between 20 and 75 years, more than 3 months after the onset of a first unilateral ischemic or hemorrhagic stroke, moderate to severe UE motor impairment (total UE score of the Fugl-Meyer Assessment [UEFMA] score between 18 and 56), no severe spasticity in any joints of the affected arm (modified Ashworth Scale score <3 in any of the affected shoulder, elbow, wrist, and fingers), able to follow instructions (Mini-Mental State Examination total score >24), no UE fractures in the past 3 months, and not simultaneously participating in other medication or rehabilitation studies. The exclusion criteria are other neurologic (i.e., epilepsy), neuromuscular, or orthopedic disease, or severe health or physical conditions that might impede participation in this study.

### Design and procedure

The study will use a single-blind randomized pretest and posttest design. Potential participants will be identified by the therapists or research assistants, and the study procedures, risks, and benefits will be explained. All participants will sign the informed consent before enrolling in this study and be allocated to the PRI or DRI groups based on a computer-generated random-sequence table (Table 1). The second author of this study ([name]) will generate the allocation sequence, enroll participants, and assign participants to interventions. Allocation concealment is ensured, as the computer-generated random codes are not released. The study will recruit 40 patients with stroke from hospital settings. Initial and outcome assessments will be administered by a well-trained and certified occupational therapist who is blinded to the group assignment, study hypotheses, and intervention of the patients. Trial participants, care providers, outcome assessors, and data analysts will be blinded after assignment to interventions. Unblinding is permissible when knowledge of the actual treatment is absolutely essential for further management of the patient.

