### Data management and quality

The documents of this study, including data recording sheets and signed informed consent forms, will be stored in a locked cabinet. The electronic database will be password-protected. Personal information of the participants will be deleted from the electronic database. The principle investigator ([name]) was in charge of data monitoring in this study. Therefore, there was no additional traditional data monitoring committee. The second author of this study ([name]) will conduct interim data analyses and the principle investigator ([name]) will make the final decision to terminate the trial.

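### One person generates the random sequence, enrols and assigns, so the stated ground for allocation concealment fails; the design also contradicts the blinding claimed for care providers and the interim analyst

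*Protocol article*

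**What the plan says.** All of the following is in the protocol article.

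- **Roles (Design and procedure).** Candidates come from clinical or research staff: "Potential participants will be identified by the therapists or research assistants". The second author then "will generate the allocation sequence, enroll participants, and assign participants to interventions", working from a random table produced by computer.
- **Concealment (same section).** "Allocation concealment is ensured, as the computer-generated random codes are not released". No independent list holder, central system or sealed envelopes is named.
- **Blinding (same section).** "The study will use a single-blind randomized pretest and posttest design". A few sentences later: "Trial participants, care providers, outcome assessors, and data analysts will be blinded after assignment to interventions". Outcome assessment is done by an occupational therapist "who is blinded to the group assignment, study hypotheses, and intervention of the patients".
- **Arms (PRI group, DRI group).** PRI starts with the forearm mode of the robot and moves to the wrist mode; DRI reverses that order. Both then receive the same impairment-oriented training.
- **Interim analyses (Data management and quality).** The second author "will conduct interim data analyses". The principal investigator is responsible for data monitoring, there is no separate monitoring committee, and the principal investigator takes the final decision on termination.

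**The concern.** Concealment requires that whoever decides whether and when a candidate enters cannot know the next assignment. The protocol gives that decision to the person who produced the sequence, and the reason it offers does not address this. If upcoming assignments are known, entry can be steered or delayed, even unintentionally. Adjustment can deal with measured baseline differences but not reliably with unmeasured ones.

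Overstated blinding is a separate problem. A reader told that participants, care providers and analysts are all blinded will give the self-reported outcomes and the interim looks more credit than the design earns. These are statements the article makes and its own design contradicts. They are not details left to a fuller document.

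**Working it through.** The article gives no figure on this point and no arithmetic applies. The check sets each claim beside the duties and procedures described elsewhere.

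1. **Enroller.** The claim is that allocation is concealed because codes are not released. The enroller generated the codes and also makes the assignments. Not releasing codes hides them from third parties only. Prior identification of candidates by therapists or research assistants does not repair this, because enrolment and assignment stay with the sequence generator. The stated reason does not support the claim.

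2. **Care providers.** The claim is that they are blinded. The PRI and DRI sections define the arms by the order of the two robot modes. Whoever runs the robot must set that order, and the order is the allocation. The claim cannot hold for that therapist.

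3. **Data analysts.** The claim is that they are blinded. The interim analyses belong to the second author, who generated the list and made the assignments. The claim fails for the interim analyses. The final analyst is not named, so nothing follows for the final analysis.

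4. **Participants.** The claim is that they are blinded. They experience which mode comes first, so they know their own order. Whether they know that order is the contrast under test, or which result is expected, is not stated. The claim is unclear rather than refuted.

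5. **Outcome assessor.** The claim is that this person is blinded. A separate therapist is described and nothing contradicts it. The claim stands.

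6. **Label.** A single-blind design is announced and four blinded parties are then listed. Both descriptions cannot be kept.

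**The case against.** Several points on the other side have force.

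- **Motive to steer is weak.** Both arms get the same robot modes, the same 45 + 45 minutes and the same training. The between-arm hypothesis runs both ways: PRI better proximally, DRI better distally. Neither arm is an inferior control, and most entry criteria are numeric (UE-FMA 18 to 56, modified Ashworth below 3, Mini-Mental State above 24). This lowers the likelihood of bias. It does not make the concealment statement true.
- **The main outcomes are better protected.** All four primary measures are administered by the blinded occupational therapist. The self-reported scales (for example ABILHAND, the Stroke Impact Scale, the Stroke Self-Efficacy Questionnaire and the Motor Activity Log interview) are secondary. This stands and narrows the harm from overstated participant blinding. Assessor blinding does not prevent selection at entry.
- **Care providers might mean other staff.** Routine-care staff, or a separate therapist giving the impairment-oriented training, could be kept unaware of the order. The text does not say so, and its plain wording includes the therapist at the robot.

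A reader might also infer more than the documents support:

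- **That the enroller knows every next assignment with certainty.** The text shows access is possible. It does not say whether the list is kept or consulted at enrolment.
- **That a false-positive rate can be attached**, by assuming a prognostic shift and applying a two-sample t test with 20 per arm. The documents give no size for any shift, and Statistical analyses plans a repeated-measures analysis of variance. If selection creates a difference d that is the same at pretest, posttest and follow-up, the between-arm difference in change is d − d = 0, and the group × time test is not inflated. The group main effect would carry d. The interaction would be biased only if selection were related to expected change.
- **That participants, or the final analyst, are certainly unblinded.** Neither is shown.

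**Conclusion.** The point holds as a contradiction in the protocol. The stated ground for concealment does not hide upcoming assignments from the enroller. Care-provider blinding cannot hold for whoever runs the robot. Analyst blinding fails for the interim analyses. The single-blind label does not match the four-party list.

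The consequence is a possible selection bias at entry, which would bear on the whole comparison of 20 against 20. Its size cannot be stated from the documents, and nothing shows that it occurred. The conclusion assumes that the person who generates the sequence can see it, and that the therapist at the robot counts as a care provider; both are the plain reading. It should be corrected because it concerns the validity of the randomised comparison, the protocol asserts the opposite, and the remedy is cheap.

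**What to change.** **Allocation**
- Have an existing team member with no role in enrolment, treatment or assessment generate and hold the list.
- Have enrolment done by staff who do not hold the list and, where possible, do not deliver the trial treatment. Treating staff see past allocations and, if blocks are used (the article does not say), could guess later ones.
- Release each assignment, from a central list or sealed numbered envelopes, only after consent, eligibility and baseline assessment are recorded.

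**Analysis**
- Have interim and final analyses run on coded arms by someone without the list.

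**Blinding statement**
- Claim blinding for the outcome assessor and, with coded arms, the analyst.
- State that treating therapists are not blinded.
- State what participants are masked to: they experience the order but may not know the hypothesis. Interpret the self-reported secondary outcomes accordingly.
- Make the design label agree with this list.

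**Reporting**
- Recruitment was due to start on December 1, 2020, before the article appeared on September 8, 2021. For anyone already randomised, report who held the list and how enrolment was actually done.

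The cost is a reallocation of duties among existing staff and a short amendment. No participants, visits or outcomes are added.
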